### Participant timeline {13}

The participant timeline is presented in Fig. 4 on the next page. Patient enrollment will occur at the T_1_ timepoint, which will also include the informed consent process, initial diagnostic interviews, and baseline symptom assessments. Following enrollment, patients will be allocated to either online EMDR or in-person EMDR therapy, with this group assignment maintained throughout the study duration. Regarding assessments:Demographic characteristics and baseline clinical features will be collected at therapy initiation (T_1_).Primary outcome measures (depression and comorbid anxiety symptoms) will be assessed at four key timepoints: baseline (T_1_), mid-therapy (T_2_), therapy completion (T_3_), and follow-up (T_4_) to evaluate temporal patterns of symptom reduction.Treatment fidelity evaluations will be conducted at the mid-therapy point (T_2_) through standardized protocol adherence checks.

**Fig. 4 Fig4:**
[figure not shown]
Patients’ timeline and schedule for enrollment, assessments, and intervention

## Data collection and management

### Plans for assessment and collection of outcomes {18a}

Primary outcomes (depression severity assessed) and secondary outcomes (anxiety symptoms measured) will be collected at four timepoints: baseline (T1), mid-therapy (T2), post-intervention (T3), and 2-month follow-up (T4). All clinical ratings will be administered by trained research assistants who are blinded to treatment allocation. The feasibility and acceptability of the online platform will be evaluated using three validated instruments, as outlined in the protocol. Treatment fidelity and therapist competence will be assessed through both qualitative and quantitative methods, also detailed in the protocol. Data integrity will be ensured through automated checks for missing values and outliers, complemented by audits conducted by the statistical analyst. Any discrepancies will prompt source document verification by an independent monitor or research assistant.

### Plans to promote participant retention and complete follow-up {18b}

To maximize participant retention and follow-up completion, a multipronged strategy will be employed, including:Regular check-in calls to address logistical or technical barriers.Flexible scheduling options, including evening and weekend sessions to accommodate working participants.A three-tiered follow-up procedure for missed appointments:Day 1: Email reminder.Day 3: Follow-up mobile/telephone call by a research assistant.Dedicated “therapy booster” sessions for patients showing signs of disengagement (defined as ≥ 2 missed appointments).Monthly retention reports, reviewed by the principal investigator to identify trends and adjust engagement strategies as necessary.

### Data management {19}

All study data will be managed using a tiered framework. Each recruited participant will be assigned a unique identification number. Physical data collected on paper will be securely stored in the principal investigator’s university archive, which is restricted and access-controlled. All study data will be archived for three years following the completion or premature termination of the trial. De-identified datasets will be retained for three years post-trial to allow for potential secondary analyses or regulatory audits. Only designated research assistants will be authorized to record and analyze data, and no other individual will be permitted to access or handle it. Role-based access permissions will be implemented, with the principal investigator having full access and research assistants granted access only to specific forms relevant to their responsibilities. All databases, including online, e.g., Google Drive, or in-system, e.g., Microsoft Excel and SPSS files, will be secured using two-factor authentication. Furthermore, Data use agreements will be mandatory for all third parties requesting access to the data, ensuring strict adherence to confidentiality and ethical standards.

### Confidentiality {27}

All data will be handled with the utmost confidentiality and will be accessible only to authorized personnel, such as the principal investigator. All participant data will be pseudo-anonymized, meaning that individuals will be identified only by a unique participant number. Any data used for publication or presentation will be fully anonymized, and only aggregated data will be reported to protect individual identities. The digital systems used for data management will include automatic session timeouts after ten minutes of inactivity and a login attempt limit of three tries to enhance data security and prevent unauthorized access.

### Plans for collection, laboratory evaluation and storage of biological specimens for genetic or molecular analysis in this trial/future use {33}

Not applicable.

### Ancillary and post-trial care {34}

All trial participants will receive appropriate post-trial care tailored to their clinical outcomes. Responders to therapy, defined as those achieving a ≥ 60% reduction in HAM-D-17 scores, will be offered two monthly booster EMDR sessions (delivered in-person or online, consistent with their assigned study arm) to reinforce treatment gains and reduce relapse risk. Non-responders will be referred to stepped-care alternatives, including medication management or evidence-based psychotherapies such as cognitive behavioral therapy, through the study’s network of collaborating psychiatric clinics. Referrals will include a summary of the participant’s trial data, shared with consent, to ensure continuity of care. For ancillary care, any unrelated medical or psychological needs identified during the trial will be addressed via referrals to local healthcare providers, with costs covered by [specify funding source: study sponsor, institutional support, or participant insurance]. Participants will be informed of these post-trial and ancillary care provisions during the consent process, including any limitations or exceptions.

## Methodology on treatment fidelity

Treatment fidelity will be established both qualitatively and quantitatively by adhering to the recommendations outlined by Dorsey et al. [76]:The psychotherapy sessions will be video recorded and reviewed by two EMDR therapy experts. Moreover, quantitative ratings of recorded sessions will be done by using predefined rating scales such as the EMDR Fidelity Rating Scale [77].The therapist’s competence will be assessed by self-reported rating scales such as the Instrument for Assessing Therapist Competence in Global Mental Health [78].Finally, patients’ satisfaction and perception about adapted DeprEnd EMDR therapy protocol will be assessed by Scale for Patient Experience of Online EMDR therapy [79] and Satisfaction with Therapy Scale [80].

## Statistical methods

### Statistical methods for primary and secondary outcomes {20a}

All quantitative analyses in Phase two and Phase three will be conducted using appropriate statistical methods aligned with the study design, outcome structure, and hypotheses. Analyses will be performed using standard statistical software (e.g., SPSS and Python 3.10+, standard statistical libraries). Phase two analyses will focus on feasibility, acceptability, safety, and preliminary symptoms change following delivery of the culturally adapted DeprEnd EMDR protocol. Feasibility indicators will be summarized using descriptive statistics, and a one-sample t-test with 95% confidence intervals and significance levels. Repeated-measures General Linear Models will be used to determine temporal symptoms changes. These analyses will be exploratory and will not be intended to establish definitive clinical effectiveness.

Phase three analyses will be conducted within a randomized controlled trial framework. First, non-inferiority is evaluated by comparing the estimated 95% confidence interval for the between-group difference to a pre-specified margin; if the upper bound lies entirely below the margin, non-inferiority is concluded [81]. For the primary outcome, non-inferiority is based on the between-group difference in change scores on the Hamilton Depression Rating Scale-17 from baseline (T1) to the end of treatment (T3), calculated as online EMDR minus in-person EMDR. A non-inferiority margin (δ) of 3 points was pre-specified a priori, consistent with previously published non-inferiority trials that defined margins on this scale [82]. For secondary outcomes of anxiety, as assessed by the Generalized Anxiety Disorder-7, between-group differences in change scores will be examined using analogous comparative principles and reported with effect estimates and confidence intervals. A non-inferiority margin (δ) of approximately 2.5 points on this scale was pre-specified a priori, informed by clinically meaningful score differences used in prior non-inferiority psychotherapy trials [83].

Furthermore, following the procedures outlined by George and Mallery [84], General Linear Model Repeated Measures (GLM-RM) analyses will be conducted to examine longitudinal changes in major depressive disorder (MDD) and comorbid anxiety symptoms across assessment time points. The GLM-RM framework will be used to test the main effect of time, the main effect of treatment group (face-to-face vs. online EMDR), and the group × time interaction, which represents differential change over time between treatment modalities. Where significant effects are observed, planned post-hoc comparisons with Bonferroni correction [85] will be performed to examine changes in symptom severity between baseline (T01) and end of treatment (T04).

Finally, to account for repeated observations nested within individuals and to examine individual variability in symptom trajectories, hierarchical linear modeling (HLM) using maximum likelihood estimation will be employed, following the analytic guidelines described by Garson [86]. In these models, Level-1 will represent repeated symptom measurements over time, and Level-2 will represent individual participants. Time will be operationalized as the number of treatment sessions from baseline to follow-up and coded sequentially (e.g., 1, 2, 3, 4, 5…). Predictor variables will be entered as covariates and examined as fixed effects (representing average effects across participants) and, where appropriate, as random effects (representing individual variability in intercepts and slopes). Given the frequent co-occurrence of depressive and anxiety symptoms [87], reciprocal associations between depression and anxiety over time will be examined using HLM-based reciprocal association methodology [77, 80] and a 1–1–1 multilevel mediation modeling approach [88, 89].

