### Clients selection and sample size {14}

The study focuses on individuals with MDD in Pakistan, specifically selecting geographically accessible participants residing in the major cities of Rawalpindi, Islamabad, and Peshawar. Recent literature cites various studies such as by Ishtiaq et al. [56], Noor et al. [57] and Umar et al. [58] on the high prevalence of depressive disorders in these three cities of Pakistan. However, since the exact number of MDD cases in these three major cities is unknown, a more customized, multi-stage sampling procedure has been adopted.

Initially, three rehabilitation centers located in the selected cities will be randomly but purposively picked for recruiting patients. The centers will not be chosen fully at random; rather, the characteristics of the vicinity and patient flow into centers will be considered. Within each selected center, clients will be recruited using a sequential consecutive sampling technique with a rolling enrollment strategy. This approach involves selecting every eligible patient who meets the inclusion criteria until the required sample size is achieved [59]. The estimated sample size of (*n* = 80) was calculated by using the below given approximation method for two independent group means, as recommended in the existing literature by Sakpal [60] and Chow [61]:$$n=\frac{\left({Z}_{\frac{\alpha }{2}}+{Z}_{\beta }{)}^{2}\cdot (2{\sigma }^{2}\right)}{\left({M}_{1}-{M}_{2}{)}^{2}\right.}$$where.

*n*= is the estimated sample size.

Zα/2 = is the Z-score matching to the desired α level (for e.g., 1.96 for 95% confidence).

Z*β* = is the Z-score matching the desired power level (for e.g., 0.84 for 80% power).

σ^2^ = is the pooled variance of two groups.

µ​_1_ - µ​_2_= are the expected difference in means of depression scores.

A two-sided significance level of α = 0.05 was selected, consistent with conventional recommendations for clinical trials, resulting in α/2 = 0.025 and a corresponding Z-score of 1.96. Statistical power was set at 80% (1 − β = 0.80), yielding β = 0.20 and a corresponding Z-score of 0.84.

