## Assignment of interventions: allocation

### Sequence generation {16a}

A covariate-adaptive randomization (minimization) approach with a random element will be employed to allocate participants in a 1:1 ratio to the intervention arms. This method is specifically designed to maintain balance across key prognostic variables in trials with moderate sample sizes and multiple baseline covariates, while preserving allocation unpredictability [64, 65]. Randomization will be implemented centrally using a pre-specified Python-based algorithm, executed by an independent research assistant following completion of baseline assessments. The algorithm evaluates imbalance across predefined covariates—including study site, gender, baseline depression severity, and psychiatric comorbidity—and assigns participants to the treatment arm that minimizes overall imbalance, with a probabilistic element (i.e., less than 100% deterministic assignment) to reduce predictability. This approach avoids the limitations of excessive stratification and fixed block randomization while ensuring transparent, reproducible, and auditable allocation. A detailed description of the randomization algorithm, operational procedures, and audit trail is provided in Supplementary File A, and Fig. 3 presents the CONSORT flow diagram illustrating participant allocation.

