### Concealment mechanism {16b}

An independent research assistant will generate the randomization sequence using covariate-adaptive algorithms accounting for age, gender, depression severity, and comorbidity, with a 1:1 allocation to treatment groups. The randomization sequence will be securely stored in password-protected documents accessible exclusively to the principal investigator and the designated research assistant, with access logs maintained for auditing purposes. Allocation concealment will be ensured until assignment, and outcome assessors and data analysts will remain blind to group allocation throughout the trial. Due to the nature of the intervention, blinding of clients to treatment delivery mode (online vs. in-person EMDR) is not feasible. Group assignment will be implemented electronically via either OpenClinica (https://www.openclinica.com) or Sealed Envelope (https://www.sealedenvelope.com) platforms, which reveal only the immediate next assignment following completion of baseline assessments. This dual protection system—combining restricted access to master randomization lists with electronic allocation masking—ensures compliance with CONSORT and SPIRIT standards for allocation concealment.

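### The two lists of minimisation factors disagree on site and age, and the primary non-inferiority contrast names no adjustment for baseline HAM-D-17 or for those factors

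*Protocol article*

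**What the plan says.** **Allocation.** Sequence generation {16a} describes minimisation with a random element, evaluated over predefined covariates that include "study site, gender, baseline depression severity, and psychiatric comorbidity". It refers to Supplementary File A (not shown) for the full algorithm. Concealment mechanism {16b} describes the same allocation as using "covariate-adaptive algorithms accounting for age, gender, depression severity, and comorbidity".

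**Primary contrast.** Section {20a} states that "non-inferiority is based on the between-group difference in change scores on the Hamilton Depression Rating Scale-17" from T1 to T3, "calculated as online EMDR minus in-person EMDR". The decision rule is "comparing the estimated 95% confidence interval for the between-group difference to a pre-specified margin", with the upper bound required to lie below it. "A non-inferiority margin (δ) of 3 points was pre-specified a priori". No model and no covariate is named for this contrast.

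**Other models in the same section.** The repeated-measures GLM has time, group and their interaction. The hierarchical model takes predictor variables as covariates but does not name them. Neither is tied to the non-inferiority test. Baseline characteristics appear in section {20c}, but as predictors in the imputation model.

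**Sizing.** Section {14} uses the formula for two independent means with an SD of 8 for change scores and a difference of 5 points. "A two-sided significance level of α = 0.05 was selected". There is no term for baseline correlation or covariates.

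**The concern.** There are two separate matters.

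First, the factor lists conflict within current text. If the list in {16b} is the one programmed, site is not balanced, although the trial runs in three centres with four therapists. If the list in {16a} is complete, age is not balanced. Either way, the reader cannot tell which factors an adjusted analysis should carry. Recruitment began on April 1, 2025, so some version is presumably already running.

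Second, minimisation on prognostic factors makes the arms more alike than simple randomisation would. An analysis that ignores those factors does not credit that balance, so its standard error is too large. A change score also fixes the coefficient on baseline at 1 instead of estimating it, which usually costs precision. Interval width matters here because, with the article's own SD and 40 per arm, the unadjusted half-width already exceeds the margin.

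**Working it through.** **1. The factor lists side by side**

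| Factor | {16a} | {16b} |
|---|---|---|
| Study site | yes | no |
| Age | not named | yes |
| Gender | yes | yes |
| Baseline severity | yes | yes |
| Comorbidity | yes | yes |

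The wording of {16a} (*including*) might leave room for age. Nothing in {16b} leaves room for site.

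**2. The plan's own sample size**

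(1.96 + 0.84)² × 2 × 64 / 5² = 7.84 × 128 / 25 = 40.14, printed as 40 per arm. It reproduces.

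**3. The contrast without adjustment**

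Inputs: SD 8 and 40 per arm from {14}; margin 3 and a two-sided 95% interval from {20a}. True difference zero is my assumption.

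- SE = 8 × √(2/40) = 1.789.
- Half-width = 1.96 × 1.789 = 3.51 points.
- Power = Φ(3/1.789 − 1.96) = Φ(−0.283) = 39%.
- 80% power would need 112 per arm.

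**4. The contrast adjusted for baseline**

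Let ρ be the T1–T3 correlation and k = SD(T1)/SD(T3). The article gives neither. The variance of the adjusted contrast relative to the change score is

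R = (1 − ρ²) / (1 + k² − 2ρk),

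which reduces to (1 + ρ)/2 when k = 1. The change-score SD is held at 8, so the half-width is 3.51 × √R and power is Φ(3/(1.789 × √R) − 1.96).

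| k (assumed) | ρ (assumed) | R | Half-width | Power |
|---|---|---|---|---|
| 1.0 | 0.3 | 0.65 | 2.83 | 55% |
| 1.0 | 0.5 | 0.75 | 3.04 | 49% |
| 1.0 | 0.7 | 0.85 | 3.23 | 44% |
| 0.7 | 0.3 | 0.85 | 3.23 | 44% |
| 0.7 | 0.5 | 0.95 | 3.42 | 41% |
| 0.7 | 0.7 | 1.00 | 3.51 | 39% |
| 0.5 | 0.3 | 0.96 | 3.43 | 40% |
| 0.5 | 0.5 | 1.00 | 3.51 | 39% |
| 0.5 | 0.7 | 0.93 | 3.38 | 41% |

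R equals 1 when ρ = k, because the regression slope of T3 on T1, ρ/k, is then exactly 1 and the change score is already the best linear adjustment.

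**5. Which k is plausible**

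Equal variances with a change-score SD of 8 imply a baseline SD of 8/√(2(1 − ρ)): 6.8, 8.0 and 10.3 at ρ = 0.3, 0.5 and 0.7. Entry requires HAM-D-17 ≥ 20 (section {26a}), and the planned severity subgroups in {20b} divide at 25/26. Spreads that large sit awkwardly with a floor of 20. The floor restricts scores at T1 but not at T3, so k below 1 is plausible.

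**6. Simulation under minimisation**

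Assumptions: 80 clients; minimisation on severity, sex, site and comorbidity with an 80/20 biased coin; only baseline severity prognostic; k = 1; 2000 runs per setting.

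| ρ | Power, unadjusted | Power, ANCOVA | Error at margin, unadjusted | Error at margin, ANCOVA |
|---|---|---|---|---|
| 0.3 | 36% | 52% | 1.7% | 2.8% |
| 0.5 | 39% | 50% | 1.7% | 2.8% |
| 0.7 | 37% | 42% | 2.5% | 3.0% |

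Nominal error is 2.5%, with simulation error of about 0.35 percentage points. The unadjusted SE averaged about 1.78, against an actual spread of the estimate of about 1.57 to 1.74. The unadjusted interval is therefore conservative. Neither estimator was biased.

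**7. The other factors**

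If site, gender, comorbidity or age explained a further 5–10% of the residual variance (assumed), power would rise by about 2 to 4 points more.

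**The case against.** The strongest reply is that the article never calls the comparison unadjusted. It fixes endpoint, direction, margin and decision rule, and a covariate set is commonly left to the analysis plan, which is not shown. A change-score endpoint is also compatible with adjustment: ANCOVA on change with baseline as covariate gives the same treatment estimate and interval as ANCOVA on T3. This stands. A reader might infer from {20a} that the primary analysis is a raw comparison that excludes baseline; the text supports only that no adjustment is named. Something remains, because the sizing formula has no baseline term and the models that could carry covariates are not linked to the non-inferiority test.

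A second reply is that the precision argument leans on equal variances at T1 and T3. This also stands: under the unequal-variance settings above, most of the gain disappears.

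A third is that {16a} says *including* and defers to a supplementary file. This stands in part. A reader might conclude that two different algorithms are specified, but the article may simply summarise one algorithm inconsistently. Which list was programmed, and so whether site is balanced, cannot be seen. The omission of site from {16b} still has to be reconciled.

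Finally, the unadjusted interval did not inflate false non-inferiority in the simulation, so this is a question of efficiency and clarity, not of validity.

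**Conclusion.** The concern holds in two limited parts.

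- **Factor lists.** The conflict over site and age is in the text and needs no assumption. It leaves unclear what is balanced and which factors a model should carry. A reader might take it as a cause of lost precision; it is not one in itself.
- **Primary contrast.** If it is analysed as written, without covariates, the interval is somewhat wider than needed. The size is uncertain: from 39% power to 44–55% with equal variances and ρ from 0.7 to 0.3, but only to about 39–44% with k of 0.5–0.7. A saving of 15–35% in sample size might be inferred from the equal-variance figures; with k of 0.5–0.7 it is 0–15%.

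Adjustment does not rescue the design. Even the most favourable row reaches 55% power and would need 73 per arm for 80%. That shortfall comes from sizing on a 5-point difference while testing against a 3-point margin, and it is a separate point.

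**What to change.** 1. Put one identical factor list in Sequence generation {16a} and Concealment mechanism {16b}, matched to the algorithm actually in use and to Supplementary File A.
2. State in {20a} that the non-inferiority contrast comes from ANCOVA, on T3 or on change, or from an equivalent mixed-model contrast, with arm, continuous baseline HAM-D-17 and the listed minimisation factors as covariates. Apply the 3-point margin to the adjusted difference.
3. Use the same approach for GAD-7, with baseline GAD-7 as the continuous covariate and its own margin of about 2.5 points.
4. Settle this before the efficacy interim at 60 participants, so that the covariates cannot be chosen with comparative results in view.

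The cost is a few sentences and a few degrees of freedom. With binary comorbidity (assumed), three sites use 2, and gender, comorbidity and baseline 1 each, with 1 more if age is kept: 5 or 6 of the 78 available with 80 clients. No new data are needed.

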### Implementation {16c}

Following eligibility confirmation and baseline assessments (T_1_), randomization will be executed through the designated electronic platform (OpenClinica/Sealed Envelope) by a research assistant who will not be involved in outcome measurement. The online system will be connected to the therapists’ and patients’ emails. It will automatically notify the treating therapist of the allocated intervention mode (online or in-person) and inform the patient via secure messaging, while maintaining the blinding of outcome assessors. To ensure protocol fidelity, therapists will receive arm-specific procedure checklists corresponding to their notification. The principal investigator will conduct weekly cross-checks between the electronic allocation records and physical randomization documents to detect and rectify any discrepancies.

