### Outcomes {12}

#### Primary outcome

The primary outcome of the study is to study the change in depressive symptom severity. It will be assessed by using the Hamilton Depression Rating Scale-17 [69]. Depression assessments will be conducted at baseline (T01), mid-treatment (T02), end-of-treatment (T03), and follow-up (T04). The primary endpoint for evaluating clinical effectiveness and non-inferiority is the change in depression scores from baseline (T01) to end-of-treatment (T03).

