### Methods for addressing non-adherence and missing data {20c}

To account for protocol deviations, primary analyses will employ both intention-to-treat and per-protocol approaches, with the intention-to-treat population including all randomized participants regardless of adherence and the per-protocol population restricted to those completing ≥ 80% of sessions with verified fidelity. For missing data, a tiered strategy will be implemented:Continuous monitoring with initiated outreach after any missed assessment to minimize attrition.Multiple imputation by chained equations using 50 imputed datasets incorporating baseline characteristics, treatment arm, and observed outcome trajectories as predictors.Sensitivity analyses comparing results with pattern-mixture models that assume different missingness mechanisms (missing at random vs. not at random).

For participants who discontinue therapy but complete all outcome assessments, their available data will be included in the mixed-effects models used for longitudinal analyses.

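### The planned group main effect in the supplementary repeated-measures model averages in the pre-randomisation baseline, so it is an attenuated quantity and not a treatment-effect estimate

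*Protocol article*

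**What the plan says.** In the Protocol article, section Statistical methods for primary and secondary outcomes {20a}, a repeated-measures general linear model follows the non-inferiority rule. Its purpose is "to examine longitudinal changes in major depressive disorder (MDD) and comorbid anxiety symptoms across assessment time points". Three terms are tested: "The GLM-RM framework will be used to test the main effect of time, the main effect of treatment group", and the "group × time interaction, which represents differential change over time between treatment modalities".

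That paragraph does not list the visits in the model, but its Bonferroni-corrected comparisons are meant "to examine changes in symptom severity between baseline (T01) and end of treatment (T04"), so baseline is a level of the time factor. Under Primary outcome, "Depression assessments will be conducted at baseline (T01), mid-treatment (T02), end-of-treatment (T03), and follow-up (T04"). Section {18a} gives the same four visits for depression and anxiety. The text under Research framework of study names only T01 to T03 for phase three.

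On timing, section Implementation {16c} says: "Following eligibility confirmation and baseline assessments (T_1_), randomization will be executed through the designated electronic platform".

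The non-inferiority decision is set separately, earlier in {20a}. It compares the 95% confidence interval for the online minus in-person difference in HAM-D-17 change from T1 to T3 with a margin of 3 points.

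**The concern.** In a repeated-measures general linear model, the between-subjects group effect compares the arms on each client's mean over all visits in the model. One of those visits here precedes randomisation, so no treatment can have acted on it. The term mixes a component whose expectation is fixed at zero with the post-baseline differences that are of interest. It answers no question about delivery mode that the trial asks.

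At stake is the reading of a supplementary result. A report that lists time, group and group-by-time tests side by side invites readers to take the group line as the overall comparison of modes. That line would understate a real difference in either direction.

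**Working it through.** **Inputs from the protocol article.** Visits T01 to T04 (Primary outcome; {18a}). Baseline before randomisation ({16c}). Baseline depression severity as a minimisation covariate ({16a}). SD of change 8, difference 5 points, 40 per arm, two-sided alpha 0.05 (Clients selection and sample size {14}).

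**The plan's own figure.** n = (1.96 + 0.84)² × 2 × 8² / 5² = 7.84 × 128 / 25 = 40.14 per arm, stated as 40. The plan gives no power or effect size for the group main effect, so there is no figure to reproduce for that term.

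**Step 1: what the term estimates.** Let d1 to d4 be the expected arm differences at the four visits. Main effect = (d1 + d2 + d3 + d4)/4. Randomisation gives d1 = 0, so this is (d2 + d3 + d4)/4 = 3/4 × (d2 + d3 + d4)/3. With T01 to T03 only, it is (d2 + d3)/3 = 2/3 × (d2 + d3)/2. These fractions hold in expectation, whatever the variances or correlations.

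**Step 2: illustration with the plan's 5 points as the T03 difference.** The course over visits is assumed.

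| Differences at T01, T02, T03, T04 | Group main effect | Mean of T02 to T04 |
|---|---|---|
| 0, 5, 5, 5 | 15/4 = 3.75 | 15/3 = 5.00 |
| 0, 2.5, 5, 5 | 12.5/4 = 3.13 | 12.5/3 = 4.17 |

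In the second row the main effect lies 37.5% below the T03 difference (1 − 3.125/5).

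**Step 3: power at 40 per arm, pattern 0, 2.5, 5, 5.** The documents give no correlation between visits. Equal correlation ρ is assumed, with the visit SD set to 8/√(2(1 − ρ)) so that the change SD is 8. Power uses noncentral t, or noncentral F for the interaction.

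| ρ | Visit SD | Group main effect | Mean of T02 to T04, unadjusted | T1-to-T3 change | Group × time |
|---|---|---|---|---|---|
| 0.3 | 6.76 | 0.84 | 0.96 | 0.79 | 0.79 |
| 0.5 | 8.00 | 0.59 | 0.80 | 0.79 | 0.79 |
| 0.7 | 10.33 | 0.33 | 0.51 | 0.79 | 0.79 |

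One cell by hand, ρ = 0.5: the variance of a client's four-visit mean is 64 × (1 + 3 × 0.5)/4 = 40. The standard error of the arm difference is √(40 × 2/40) = 1.41, and 3.125/1.41 = 2.2, which gives power of about 0.59.

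Under equal correlation, the squared signal-to-noise ratio of the main effect relative to the post-baseline mean is (3/4)(1 + 2ρ)/(1 + 3ρ). This is 0.63, 0.60 and 0.58 at the three correlations and is below 1 for every ρ from 0 to 1. Against the plan's own T1-to-T3 change test the ordering is not fixed: the main effect has more power at ρ = 0.3 and less at 0.5 and 0.7.

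**The case against.** The best defence is that the same sentence supplies the right term. It assigns differential change between modes to the group-by-time interaction, which baseline does not dilute and which keeps power of 0.79 above. The repeated-measures model is also supplementary. It comes after the non-inferiority rule and chiefly serves hypothesis iii, on symptom reduction over time. Both points stand and limit the reach of this one. They do not turn the group main effect into a treatment comparison. It remains a separately planned test, and the interaction is an omnibus test that gives no arm difference at any visit.

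Two stronger readings are tempting. The first is that the diluted test tilts the trial towards a finding of no difference between modes. The document does not support this: non-inferiority is decided on the confidence interval for T1-to-T3 change, and nowhere is a non-significant group effect said to mean equivalence. Misreading is a risk, not a stated rule.

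The second is that this model will drop every client with a missed visit and so bias the result. Standard software does require complete rows. But section {20c} plans multiple imputation with 50 datasets, and for clients who stop therapy yet complete all assessments, "their available data will be included in the mixed-effects models used for longitudinal analyses". Which data feed the repeated-measures model is not stated, and a condensed article may leave that to the full plan.

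**Conclusion.** The point holds for one term of a supplementary phase-three analysis. The group main effect is in expectation three quarters of the mean post-baseline difference with four visits, or two thirds with three, and should not be reported as an effect of delivery mode. The fractions rest only on baseline being a level of the time factor, which the post-hoc contrasts imply, and on baseline preceding randomisation, which is stated. The power figures rest on an assumed correlation structure and an assumed course of the difference; they show scale only. The primary non-inferiority conclusion and the interaction test are not affected by this dilution.

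**What to change.** Remove the group main effect as a test between modes. In its place, report the online minus in-person difference with a 95% CI at T2, T3 and T4 from a mixed model with visit as a categorical factor, arm by visit, and baseline score as covariate, including all randomised clients. A longitudinal model that keeps T1 as an outcome with a common mean in both arms would serve equally well.

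Keep the time effect and the within-arm change-from-baseline contrasts, which hypothesis iii needs. When doing so, align the visit label: {20a} calls T04 the end of treatment, while Primary outcome gives that name to T03 and makes T04 the follow-up. Add a sentence that a non-significant group or interaction test is not evidence of non-inferiority.

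This is a modified model, not the hierarchical model already planned, which codes time by session number. The cost is a small amount of extra analysis and revised wording, with the same data and software.
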